### Trial design {8}

This study is a phase IIb randomised, double-blind clinical trial type study. It will be a parallel design where two groups receive two treatments (interventions). We will study the characteristics of the factors and effects. In this manner, this analysis will allow us to conceptualise the design as a 2 × 3 mixed factorial. Thus, we will include a factor between groups (type of intervention, two levels) and an intra-subject factor (measured in three episodes, one pre-intervention, and two post-intervention). Based on the factor between groups, it will implement two different interventions. The treatment group will receive a cognitive training intervention combined with alternating current electrical stimulation (i.e. treatment). The control group will receive a traditional cognitive training intervention with placebo electrical stimulation. Depending on the intra-subject factor, two dependent variable measurements will be implemented: one pre-intervention and one post-intervention measure. This design will allow the study of the potential interaction effects between the inter- and intra-subject factors [35].

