### Intervention description {11a}

In the CCTP, the patients will be organised into groups composed of three participants. The patients will realise a combined electrical stimulation and cognitive training programme. That contemplates 12 WM training sessions based on tasks of storage and manipulation of verbal and visuospatial information, with a frequency of twice a week for 6 weeks, completing a total of 12 sessions in presential format. Concomitantly, the participants will receive real electrical stimulation for 10 min during a verbal working memory task. The intervention will be delivered by trained personnel in this technique and an assistant to groups. This electrical stimulation protocol includes 10-s periods of phase-in and 10 s of phase-out and will be done in parallel with the cognitive intervention programme in sessions 3, 4, 5, 6, 7, 8, 9, and 11. The electrical stimulation will be applied with two 3 × 1 arrays of electrodes. The central stimulation electrodes will be positioned in F3 and CP3 (according to the international 10–20 system). The AC stimulation will be one mA from the baseline to the stimulation peak. The stimulation will have a gamma sine waveform (80 Hz) over the positive phase of the theta oscillation[33] individualised for each patient ranging from 4 to 8 Hz and the phase-locked between arrays [36, 37]. The electrode impedances will always be maintained under 10 kOhms.

Participants in the control group (TCTP) will start a cognitive intervention programme identical to the treatment group and will be organised into groups of three participants. Still, unlike the treatment group, they will receive placebo electrical stimulation, i.e. an electrical current will be applied for a short period at the beginning of the session (30 s). Then, the electric stimulation will be stopped. This procedure induces a sensation in the skin similar to real electric stimulation without generating a detectable impact on the brain state. They will be performed parallel to the cognitive intervention programme in sessions 3, 4, 5, 6, 7, 8, 9, and 11.

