## Assignment of interventions: allocation

### Sequence generation {16a}

Individual participants will be allocated to either CCTP or TCTP at a 1:1 ratio through remote randomisation by the staff responsible for randomisation at the Biomedical Informatics Center Clinica Alemana—Universidad del Desarrollo, Chile (CIMB) (https://redcap.cibm.cl). The clinical trial will use the stratified randomisation method, with age (< 75 years and ≥ 75 years), sex (male and female), and years of schooling (≤ 12 years of education and > 12 years of education) as the stratification variables. Randomisation will be performed under the control of a blinded worker from CIMB, who is the only person allowed to manage the electronic coding of the randomisation to assign the individuals. The researchers will be blind to the group to which the participant is allocated.

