#### Inferential analysis

Compliance with assumptions for parametric testing will be contrasted. In particular, univariate normality (i.e. Kolmogorov-Smirnoff, Shapiro–Wilk), sphericity (i.e. Mauchly’s W), and homoscedasticity of error variances (i.e. Levene test). If any of the above assumptions are violated, the corresponding non-parametric estimates will be provided. Mixed-model analyses without any ad hoc imputations will be used to handle missing data in case of participant drop-out and to conduct the efficacy analysis [53]. To assess distributional assumptions and the impact of missing random effect components on the model, several tests will be conducted. Normality assumptions will be examined using the Shapiro–Wilk test, skewness and kurtosis indices, and normality plots (Q-Q plots). Homoscedasticity will be investigated using Levene’s test and Box’s M test for equivalence of covariance matrices. The Wald statistic (or *Z*-test) will be utilised to test residual error variance estimation and the null hypothesis of homogeneity of residuals. The assumption that data is missing completely at random (MCAR) will be assessed using Little’s MCAR test, which remains robust to violations of distributional assumptions [54]. Additionally, the primary outcome will be evaluated using Bayesian hierarchical approaches employing JAGS and R software. In this approach, each individual beta per regressor will be subjected to a population distribution of beta values that follow a normal distribution [55]. The prior assumption for each population distribution of beta values will be flat (non-informative). The correct convergence of the Markov Chain Monte Carlo (MCMC) will be evaluated using the Gelman-Rubin statistic. The model fit will also be assessed using DIC (Deviance Information Criterion) and LOOIC (Leave-One-Out Information Criterion).

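### The stated arm-by-time analysis does not reflect the stratified randomisation or the same-arm training trios, and it uses baseline inefficiently

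*Protocol article*

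**What the plan says.** **Analysis structure.** Trial design {8} sets out a 2 × 3 mixed factorial: "we will include a factor between groups (type of intervention, two levels) and an intra-subject factor". The repeated factor is "measured in three episodes, one pre-intervention, and two post-intervention", so baseline is a level of the outcome. The same paragraph later says "two dependent variable measurements will be implemented: one pre-intervention and one post-intervention measure", which conflicts on the number of measurements; on either reading baseline is in the outcome. The hypothesis is a larger pre-to-post increase in the combined arm. Sample size {14} is based on the interaction in a 2 × 2 mixed ANOVA. Inferential analysis keeps the repeated-measures ANOVA apparatus (Mauchly, Greenhouse-Geisser, partial eta squared, Friedman as fallback) and adds that "Mixed-model analyses without any ad hoc imputations will be used" for drop-out and efficacy.

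**Randomisation.** Sequence generation {16a}: "Individual participants will be allocated to either CCTP or TCTP at a 1:1 ratio", and "The clinical trial will use the stratified randomisation method". Three factors are named: age split at 75, sex, and schooling split at 12 years. With two levels each, that is 8 strata.

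**Delivery.** Intervention description {11a} says of the combined programme that "the patients will be organised into groups composed of three participants". It arranges the control programme in threes as well. The trios are therefore nested within arm, for 12 sessions.

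No statistical section mentions a stratification factor, a baseline covariate or a training-group term. The Bayesian hierarchy is over individuals' regression coefficients, not over trios.

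**The concern.** Three features of the design bear on the precision of the arm comparison, and the stated analysis uses none of them well.

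- **Baseline.** When baseline is a level of time, the arm-by-time interaction is a comparison of change scores. Under randomisation this is valid, but it is never more efficient than adjusting for baseline.
- **Strata.** Factors used to balance the arms should be in the model. If they predict the analysed quantity and are left out, the reported standard error is too large.
- **Trios.** Individuals are randomised but treated in groups in both arms. If outcomes within a trio are correlated, an analysis that treats participants as independent reports a standard error that is too small.

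With 62 participants, precision that can be had from data already collected is worth having, and a test that may be anti-conservative should be protected.

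**Working it through.** **1. The plan's own sample size.** Inputs from Sample size {14}: eta² = 0.06, power 0.95, alpha 0.05, two measurements. The pre-post correlation is not stated; 0.5 is assumed, the software default.

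f² = 0.06/0.94 = 0.0638. Noncentrality = 54 × 0.0638 × 2/(1 − 0.5) = 13.8, on 1 and 52 df. Power = 95.4%, so 54 is reproduced. It treats participants as independent.

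**2. Baseline.** With unit variance and pre-post correlation rho, the change score has variance 2(1 − rho) and the baseline-adjusted value 1 − rho². Their ratio is (1 − rho²)/[2(1 − rho)] = (1 + rho)/2.

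| rho (assumed) | Change | Adjusted | Ratio |
|---|---|---|---|
| 0.3 | 1.40 | 0.91 | 0.65 |
| 0.5 | 1.00 | 0.75 | 0.75 |
| 0.7 | 0.60 | 0.51 | 0.85 |

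At rho = 0.5, 1/0.75 = 1.33: adjustment is worth about a third more participants, or 54 × 0.75 = 40.5 (about 41) in place of 54.

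**3. Strata and trios.** With two visits and complete data, the arm-by-time test is a two-sample t-test on change, so that test was simulated at nominal 5%: 27 per arm, 9 trios per arm, one balanced stratification factor, 10,000 runs (Monte Carlo error about 0.2 points). ICC is the trio intraclass correlation and R² is the share of the variance of change explained by the stratum. The documents give neither, so all values are assumptions.

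| ICC | R² | True SE | Mean reported SE | Type I error |
|---|---|---|---|---|
| 0 | 0 | 0.272 | 0.271 | 5.0% |
| 0.05 | 0 | 0.287 | 0.270 | 6.3% |
| 0.10 | 0 | 0.302 | 0.270 | 7.7% |
| 0.20 | 0 | 0.319 | 0.269 | 9.4% |
| 0 | 0.10 | 0.257 | 0.272 | 3.8% |
| 0 | 0.20 | 0.243 | 0.272 | 2.8% |
| 0.05 | 0.10 | 0.273 | 0.271 | 5.2% |
| 0.10 | 0.10 | 0.281 | 0.271 | 5.6% |
| 0.10 | 0.20 | 0.266 | 0.271 | 4.8% |

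A separate simulation with 10 trios per arm (40,000 runs, no stratum effect) gave 6.3%, 7.3% and 10.0% at ICC 0.05, 0.10 and 0.20.

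**4. Effect of trios on power.** Dividing the noncentrality by the design effect 1 + (3 − 1) × ICC, power at 54 becomes 93.5%, 91.4% and 86.9% at ICC 0.05, 0.10 and 0.20.

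**5. Which trio term works.** A shared-training effect can arise only after baseline. Take 10 trios of 3 per arm, rho = 0.5, and a trio effect at the post visit only with ICC 0.20. After baseline adjustment the residual variance is 0.75, of which 0.20 is trio variance.

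- SE assuming independence: √(2 × 0.75/30) = 0.224.
- True SE: √[2 × (0.55/30 + 0.20/10)] = 0.277.

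In simulation (700 runs, constrained baseline), a trio intercept constant over all visits gave a mean SE of 0.221 against a true 0.276 and rejected 9.9%; with no trio term the rate was 11.3%. At ICC 0.10 the rates were 7.7% and 8.0%. A trio effect restricted to post-baseline visits held the level at about 4-5%. A second simulation with the constant intercept at ICC 0.20 agreed in direction: mean SE 0.254 against a true 0.296.

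Baseline adjustment also raises the trio share of what remains (0.20/0.75 = 0.27), so the trio term matters more once baseline is adjusted for.

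**The case against.** The strongest reply is that the efficacy model is not written out. The two-factor description is in the design section; the Inferential analysis section names a mixed model without listing its fixed or random terms, and no passage excludes covariates or a group effect. Such detail is commonly left to an analysis plan, which is not shown. This stands against any claim that the model contains only arm and time. It does not remove the point: the article commits to an arm-by-time factorial in its design, hypothesis, sample size and assumption checks, and that structure does not match the design stated in the same document.

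Four further replies also have force:

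- **Baseline as an outcome is not an error.** The interaction directly tests the stated hypothesis and its standard error is valid. The loss is of efficiency only.
- **A stratum effect that is constant over time cancels in the change score.** Only strata that predict change matter, and the article reports no such association.
- **The trio correlation may be close to zero.** The primary outcome is an individual electroencephalographic measure and the stimulation frequency is individualised. The article does not say that a trio keeps one trainer.
- **The two standard-error effects can nearly cancel**, as the 4.8% to 5.6% rows show. But the sizes are unknown, so cancellation cannot be relied on.

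**Conclusion.** The point holds in a conditional form. The stated arm-by-time analysis reflects neither the stratification nor the same-arm trios, and it forgoes precision from baseline.

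The baseline gain rests only on the pre-post correlation: adjusted variance is 65% to 85% of the change-score variance for correlations of 0.3 to 0.7. The trio effect requires a positive intraclass correlation: type I error of about 6%, 7-8% and 9-10% at 0.05, 0.10 and 0.20 if strata play no part. The strata effect requires that they predict change: type I error of 3.8% and 2.8% at R² of 0.10 and 0.20 if trios play no part.

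A reader might infer that the planned standard errors are wrong in both directions. The documents do not support that: they give neither an intraclass correlation nor a stratum association, and the effects may offset. Nor do they support reading this as showing the trial underpowered. On the plan's own inputs (with the assumed 0.5 correlation), power at 54 is 95.4%, and 86.9% at an intraclass correlation of 0.20.

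**What to change.** Specify the primary model as a baseline-adjusted longitudinal model, either ANCOVA-type or with a baseline mean constrained to be equal across arms. Include arm-by-visit effects after baseline and fixed effects for age group, sex and schooling group. If baseline stays in the outcome vector, let the stratum effects differ by visit; otherwise they do not adjust for prediction of change.

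Record trio membership, and include a trio random effect that acts on the post-baseline visits only, with small-sample degrees of freedom (Kenward-Roger or Satterthwaite), as the primary or a sensitivity analysis. Do not use a trio intercept constant over all visits: it leaves the inflation almost unchanged. Since 31 per arm does not divide by three (10 trios and one person over), state how incomplete groups are coded.

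The cost is analysis-plan wording and one database field, which should be captured while sessions run. The statistical price is a few degrees of freedom, and a somewhat wider interval if trio correlation is present.

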## Methods: participants, interventions, and outcomes

### Study setting {9}

The target population will be non-institutionalised patients with MCI referred to the Center of Phonoaudiological Attention of the University of Valparaiso (CAFUV) from Valparaiso, Chile. Assessments will be conducted on site by a clinical team consisting of a neuropsychologist, a clinical psychologist, and speech therapists at the research centre, who will apply the instruments to corroborate the fulfilment of the inclusion–exclusion criteria.

### Eligibility criteria {10}

We will recruit participants diagnosed with mild cognitive impairment (MCI).

*Inclusion criteria* will be:MCI diagnostic, according to the criteria established by Petersen et al.[13].Age equal to or greater than 60 years.Six or more years of complete schooling (presence of reading and writing).

Potential participants will be excluded if:The previous diagnosis of other neurodegenerative diseases.Attending another cognitive training programme.A history of epilepsy or the current presence of epileptic seizures.The presence of psychiatric diseases.The presence of a relevant depressive picture (GDS >  = 2).History of important neurological alterations such as the history of stroke, transient ischemic attack, and cranial brain trauma.Significant alterations of communication.

### Who will take informed consent? {26a}

Informed consent will be obtained through a two-phase process. Participants will first receive information from their clinical team. They will then grant permission for the research team to contact them for an initial discussion of the study and screening process. A study researcher will obtain full informed consent before the eligibility and baseline assessment, which will be conducted in person. Potential participants will receive complete information about the study before the interview, and at the point of consent, there will be additional opportunities to discuss the research and for participants to ask any questions. The option to withdraw from the trial will be fully explained, and researchers will be trained in obtaining informed consent, including assessing capacity to consent where appropriate and supervised by the CI. Consent will only be obtained from individuals capable of making an informed decision regarding their participation.

### Additional consent provisions for collecting and using participant data and biological specimens {26b}

On the consent form, participants will be asked if they agree to be contacted about ethically approved research studies for which they might be suitable. Participants will also be asked if they agree to their anonymised data, anonymised transcripts, and session recordings being used in future research. For more details, see the copy of the consent form at the end of this article. This trial does not involve collecting biological specimens.

## Interventions

### Explanation for the choice of comparators {6b}

A combined cognitive training programme (CCTP) was chosen as a comparator to study the most significant effect potential concerning a traditional cognitive training programme (TCTP) in treating patients with MCI.

### Intervention description {11a}

In the CCTP, the patients will be organised into groups composed of three participants. The patients will realise a combined electrical stimulation and cognitive training programme. That contemplates 12 WM training sessions based on tasks of storage and manipulation of verbal and visuospatial information, with a frequency of twice a week for 6 weeks, completing a total of 12 sessions in presential format. Concomitantly, the participants will receive real electrical stimulation for 10 min during a verbal working memory task. The intervention will be delivered by trained personnel in this technique and an assistant to groups. This electrical stimulation protocol includes 10-s periods of phase-in and 10 s of phase-out and will be done in parallel with the cognitive intervention programme in sessions 3, 4, 5, 6, 7, 8, 9, and 11. The electrical stimulation will be applied with two 3 × 1 arrays of electrodes. The central stimulation electrodes will be positioned in F3 and CP3 (according to the international 10–20 system). The AC stimulation will be one mA from the baseline to the stimulation peak. The stimulation will have a gamma sine waveform (80 Hz) over the positive phase of the theta oscillation[33] individualised for each patient ranging from 4 to 8 Hz and the phase-locked between arrays [36, 37]. The electrode impedances will always be maintained under 10 kOhms.

Participants in the control group (TCTP) will start a cognitive intervention programme identical to the treatment group and will be organised into groups of three participants. Still, unlike the treatment group, they will receive placebo electrical stimulation, i.e. an electrical current will be applied for a short period at the beginning of the session (30 s). Then, the electric stimulation will be stopped. This procedure induces a sensation in the skin similar to real electric stimulation without generating a detectable impact on the brain state. They will be performed parallel to the cognitive intervention programme in sessions 3, 4, 5, 6, 7, 8, 9, and 11.

### Criteria for discontinuing or modifying allocated interventions {11b}

Participants can withdraw at any point if a participant in either arm indicates that they wish to discontinue the trial. In this case, they will only be contacted further by the research team to invite them to take part in a brief written survey to ascertain their reasons for not taking part. However, the participants will have no intermediate levels of discontinuation of the trial.

We will assess whether it is in the participant’s best interest to continue or discontinue trial treatment if a serious adverse reaction occurs. In such cases, discontinuation of the intervention will be recommended. If an unexpected serious adverse reaction is linked directly to trial participation or treatment, the trial will be temporarily halted for investigation. If future risk cannot be mitigated, the trial will be discontinued. The sponsor, ethics committee chair, and principal investigator will lead this process. The same protocol will be followed if information surfaces indicating that the therapy intervention or trial procedures are unsafe.

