## Statistical methods

### Statistical methods for primary and secondary outcomes {20a}

Both the intention-to-treat (ITT) analysis set and the per-protocol (PP) analysis set will be utilised. The ITT set comprises all participants who have been randomised. When a participant is randomly assigned to a combining cognitive training group, they should be included in the combining cognitive training analysis. For the PP set, only participants who complied with combining cognitive training will be analyzed. The ITT analysis will be compared with the PP analysis to ascertain whether the two results are consistent.

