### Methods in analysis to handle protocol non‐adherence and any statistical methods to handle missing data {20c}

The statistical analyses, including mixed models and Bayesian estimation, will be conducted without resorting to ad hoc imputations to manage missing data resulting from participant drop-out and to perform efficacy analysis. Little’s MCAR test will determine whether the missing data are completely at random, ensuring the robustness of the analyses even without data imputation.

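### Withdrawal ends outcome collection, so the ITT analysis rests on a missing-at-random assumption that Little's test cannot secure, and the per-protocol set, worded for one arm, cannot check it

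*Protocol article*

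**What the plan says.** **Stopping.** Under Criteria for discontinuing or modifying allocated interventions {11b}, a participant in either arm who wishes to leave the trial is handled as follows: "they will only be contacted further by the research team to invite them to take part in a brief written survey". The paragraph closes by saying that "the participants will have no intermediate levels of discontinuation of the trial". The next paragraph deals with a different event, a serious adverse reaction, and speaks of trial treatment rather than the trial: "In such cases, discontinuation of the intervention will be recommended". It does not say whether the later assessments still take place.

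**Assessments at stake.** Participant timeline {13} places the post-intervention assessments at 1 week and 12 weeks.

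**Analysis sets.** Statistical methods for primary and secondary outcomes {20a} states: "The ITT set comprises all participants who have been randomised". It then states: "For the PP set, only participants who complied with combining cognitive training will be analyzed". No compliance rule is given for the traditional-training arm (TCTP). The two sets are put to this use: "The ITT analysis will be compared with the PP analysis to ascertain whether the two results are consistent".

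**Missing data.** Inferential analysis says: "Mixed-model analyses without any ad hoc imputations will be used to handle missing data in case of participant drop-out". Section {20c} repeats this and says Little's MCAR test will settle whether data are missing completely at random, "ensuring the robustness of the analyses even without data imputation".

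**The concern.** Three statements interact.

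1. Someone who finds the sessions too much has no stated way to give them up and still attend the outcome visits. Their later outcomes are never collected, and no analysis can recover them.
2. The ITT analysis must therefore infer those outcomes from the observed data, which is valid under MAR. The article does not state that assumption. It offers Little's test as assurance, and that test addresses a different and stricter condition, MCAR.
3. The remaining safeguard is the comparison with the PP result. If PP removes non-compliers from the combined arm (CCTP) only, it compares a selected group with an unselected one. Agreement or disagreement with ITT then says little about either.

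What is at stake is the credibility of the arm contrast on prefrontal theta if drop-out turns out to differ between arms or to depend on unseen outcomes.

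**Working it through.** **Inputs from the article (Sample size {14}):** η² = 0.06, power 0.95, α = 0.05, N = 54, drop-out about 15% with no split by arm or by time, enrolled N = 62 (31 per arm).

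**Step 1. The plan's own figure.** Take the within-between interaction of a 2 × 2 mixed ANOVA with m = 2 measurements. The correlation ρ = 0.5 and sphericity are assumed, since the article gives neither.

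- f² = 0.06/0.94 = 0.0638; λ = f²·N·m/(1 − ρ) = 0.0638 × 54 × 2/0.5 = 13.79; df = 1 and 52.
- Power is 0.954 at N = 54, the smallest even N reaching 0.95. The stated 54 is reproduced.
- Setting λ = N·d²/4 gives an implied difference in change of d = √(4 × 0.0638 × 2/0.5) = 1.01 SD.

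**Step 2. How many outcomes are exposed.** 62 × 0.15 = 9.3, so about 9 participants; 62 × 0.85 = 52.7 remain. Power is 0.947 at N = 52 and 0.950 at N = 53, so precision is hardly touched. The issue is validity. Nine is an upper figure: anyone who leaves after the 1-week visit keeps that value.

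**Step 3. ITT on observed data.** Let q1 and q2 be the shares lost in CCTP and TCTP, and let g be the gap in mean change (in SD) between those who stay and those who leave. The observed mean in an arm exceeds the full-arm mean by q·g. If the model cannot explain g from observed data, the contrast is off by g·(q1 − q2). The values of q and g are assumed.

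| Drop-out, CCTP vs TCTP | g = 0.5 | g = 1.0 |
|---|---|---|
| 15% vs 15% | 0 | 0 |
| 20% vs 10% | 0.05 SD | 0.10 SD |
| 25% vs 5% | 0.10 SD | 0.20 SD |

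**Step 4. PP filtered in one arm.** If a share q of CCTP is removed and no one in TCTP, the bias is q·g. For the error rate, SE = √(1/(31(1 − q)) + 1/31) in SD units, and the two-sided normal test at 1.96 is evaluated with no true effect. The values of q and g are again assumed.

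| q removed | g | Bias | Type I error |
|---|---|---|---|
| 5% | 0.25 | 0.0125 SD | 0.050 |
| 15% | 0.5 | 0.075 SD | 0.059 |
| 15% | 1.0 | 0.15 SD | 0.087 |
| 20% | 1.0 | 0.20 SD | 0.115 |

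**Step 5. What a non-significant MCAR check is worth.** As a proxy, take a two-sample t-test of one baseline variable, 9 drop-outs against 53 others, df = 60, noncentrality d·√(9 × 53/62). Power is 0.13, 0.28 and 0.59 for true differences of 0.3, 0.5 and 0.8 SD. This is not Little's test itself, but it shows how little 9 drop-outs can reveal. There is also a limit that sample size does not remove: the test uses observed values only, so it cannot separate MAR from MNAR.

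**The case against.** **The ITT analysis is sound in principle.** It covers everyone randomised and uses every observed value, and a mixed model is unbiased for its target under MAR. A reader might infer from the withdrawal rule that neither set gives an unbiased comparison. The documents do not support that: they give no drop-out by arm, and Step 3 shows zero bias when drop-out and gaps are equal. Dependence on an untestable assumption is a risk and not a demonstrated bias.

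**Not everyone who stops is lost.** The survey-only rule is written for those who wish to leave the trial. For treatment stopped after a serious adverse reaction the section is silent on assessments, so it would be wrong to say that anyone who stops loses all outcomes. This narrows the point, but the two paragraphs still need reconciling.

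**The PP sentence may be loose wording.** Both arms receive the same training programme, the preceding ITT sentence also names only the combined group, and a set without controls could not be compared with ITT. This is a fair reading of the intent. Combined training is nevertheless the name of one arm, and the sentence as written supplies no rule for the other.

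**The sizes are modest.** The largest assumed bias, 0.20 SD, compares with a design difference of about 1.01 SD. A reader might also suppose that those who stop gain nothing, so that completers overstate the effect by a fixed proportion. Nothing in the article supports that assumption.

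**Some elements belong in an SAP.** Which set is primary, the attendance threshold and a sensitivity analysis may be set out there, and their absence here is not held against the plan. The objection does not reach the withdrawal rule, the one-arm PP wording or the robustness claim, all of which the article states itself.

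**Conclusion.** The point holds in a limited form, as something that should be changed.

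- **Withdrawal rule.** Participants who wish to stop have full exit as their only route, and the section is unclear about assessments when only treatment is stopped. Up to about 9 of 62 participants may lack post-withdrawal outcomes. The ITT result then relies on MAR, with a potential bias of 0 under equal drop-out and gaps, and 0.05 to 0.20 SD under the assumed unequal rates in Step 3.
- **Little's test.** The claim that it secures robustness is wrong. It cannot verify MAR, and at this size a non-significant result is weak evidence even about MCAR.
- **PP set.** Taken literally it filters CCTP only, with a bias of about 0.01 to 0.20 SD and type I error of 0.050 to 0.115 for 5% to 20% removed and gaps of 0.25 to 1.0 SD. It cannot serve as the consistency check on ITT.

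The counts follow from the article's own 15%. The bias sizes rest on the assumed shares and gaps and are not predictions.

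**What to change.** 1. **Section {11b}.** Reconcile the two paragraphs, and separate stopping the sessions from withdrawing from assessments. Participants who stop sessions would be invited, with their consent, to the scheduled 1-week and 12-week assessments. Cost: a short amendment and a few more attendances at visits for which reminder calls and transport are already planned. Some will decline. Because Trial status projected recruitment to close on January 26, 2024 and the study to end on December 30, 2024, the change helps only participants still in the trial.
2. **Section {20a}.** Define PP by one session-compliance rule applied identically to CCTP and TCTP, counting active and placebo sessions alike, and describe PP as supportive to ITT. Cost: wording only, settled before unblinding.
3. **Section {20c}.** Delete the statement that the MCAR test secures robustness. State that the mixed model assumes MAR, and examine departures from it with a delta-adjusted sensitivity analysis, shifting the assumed outcomes of drop-outs by arm and reporting where the conclusion changes. If the SAP already contains this, refer to it. Cost: some programming and no new data.
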